## Abstract

**Background**: Loneliness in later life is often addressed with befriending interventions, yet evidence for their effectiveness is limited. Meanwhile it is known that loneliness has a deleterious impact on health. The aim of the study is to evaluate whether a befriending service for older adults mitigates the impact of loneliness on health outcomes, and to identify mechanisms through which befriending interventions might impact upon health.

**Methods**: A mixed methods design is used. The quantitative component utilises an AB single-case experimental design, to gather intensive longitudinal data. These data will be analysed using a generalised additive modelling approach. The qualitative component of the study uses semi-structured dyadic interviews, structured and analysed according to the principles of constructivist grounded theory. Findings will then be triangulated according to an existing mixed methods integration protocol.

**Discussion**: This mixed methods design has the potential to inform national and international policy in relation to befriending interventions for older adults. In addition, there is the potential for study results to inform our theoretical understanding of the nature of the relationship between loneliness and health.

**Trial registration:** ClinicalTrials.gov identifier
NCT04301167 (10
^th^ March 2020). Protocol version 1.1, 26
^th^ June 2020.

## Introduction

Befriending services are often used to provide social connection to individuals who are socially isolated. The service typically involves trained volunteers being matched with a service user in a structured manner, e.g. for weekly visits. Befriending services may improve health, since elective relationships have a positive impact on health (
Golden *et al.*, 2009). Befriending services have also been shown to reduce loneliness (
Lawlor *et al.*, 2014). Befriending may also benefit brain health, since social relationships are associated with a reduced risk of developing dementia (
Kuiper *et al.*, 2015;
Morley *et al.*, 2015). A relatively new term, brain health refers to the preservation of optimal mental and cognitive function in the face of age-related decline, and in the absence of disease-related decline (
Wang *et al.*, 2020). 

However, the theoretical basis for how befriending might impact health is poorly understood (
Lester *et al.*, 2012). The causal cascade model has been used to explain the impact of social engagement on health (
Berkman *et al.*, 2000) and cognitive decline (
Zunzunegui *et al.*, 2003) and could constitute a model of the relationship between befriending and brain health. In this model, social engagement confers a health benefit to individuals at a series of levels from the macro (cultural norms, urbanisation), the mezzo (social network size, reciprocity of ties) to the micro (emotional social support, intimate contact), which all influence health or cognitive functioning via behavioural (e.g. help-seeking behaviour, diet), psychological (e.g. self-esteem), and physiological (e.g. immune system function, allostatic load) pathways.

Befriending may improve health partly via its effect on loneliness (
McGoldrick *et al.*, 2017), which affects 10% of older Irish adults (
Harvey & Walsh, 2016). Reducing loneliness is a desirable outcome because of its associations with various undesirable outcomes including depression (
O'Luanaigh & Lawlor, 2008), dementia (
Wilson *et al.*, 2007) and poor quality of life (
Ekwall *et al.*, 2005). Researchers have predicted that befriending services could reduce dementia by 0.21% through reducing loneliness (
Owen *et al.*, 2016). However, this prediction has not been formally evaluated.

As has been highlighted previously (
Harvey & Walsh, 2016), loneliness has mostly been ignored in Irish health policies, and services that address loneliness are not delivered in a centralised or coordinated fashion. This situation differs to the UK, where a befriending sector is established, alongside a
national campaign to end loneliness, which
*inter alia* promotes befriending to decrease loneliness. Members of the research team have previously designed and evaluated two psychosocial interventions, one of which found that befriending alleviated loneliness (
Lawlor *et al.*, 2014). We also evaluated an existing befriending service and found that it was perceived as an effective way to reduce loneliness (
[name] *et al.*, 2015).

The proposed research is timely since it responds to recommendations made in the Institute of Public Health’s recent report on loneliness in Ireland (
Harvey & Walsh, 2016), and to an evaluation finding that Ireland has poor availability of services to reduce loneliness (
Burke, 2015) as well as recent efforts to martial government funding towards loneliness services (
Loneliness Taskforce). The research will add to the scientific evidence base for use of befriending interventions to improve health, and will help elucidate the mechanisms through which befriending improves health. Existing theories provide a clear scientific rationale for hypothesising that befriending will impact health, and may moderate the impact of loneliness on health.

### Aims and objectives

**Overall study aim:** To improve understanding of the health-related impacts of befriending on older adults, and to understand the role of loneliness in this regard.

**Hypothesis 1:** Befriending services have a positive impact on health-related quality of life and brain health.

**Hypothesis 2:** Receipt of a befriending service moderates the negative impact of loneliness on health-related quality of life and brain health.

**Objective of qualitative component:** To explore potential mechanisms by which befriending impacts health in a series of dyadic and individual semi-structured interviews with recipients of a befriending service and their partnered befrienders.

## Methods

This study was registered retrospectively on ClinicalTrials.gov (identifier
NCT04301167) on 10
^th^ March 2020. As per ClinicalTrials.gov guidelines, registration can be completed at any point during the project lifespan except in the case of medical trials. In the case of the current study, registration was delayed because of staffing issues.

### Design and study setting

The study uses a mixed methods design. Quantitative methods are used to investigate whether befriending moderates the impact of loneliness on health-related quality of life and brain health. Qualitative methods are used in an exploratory supplementary fashion to explore potential mechanisms through which befriending impacts health. A mixed methods analysis will triangulate and integrate findings across the quantitative and qualitative approaches to arrive at an empirically justifiable theory of the mechanisms through which befriending might impact health. For the quantitative study component, participants can choose to have their initial informed consent meeting in their homes or in testing suites in the host research institution. Participants are eligible if they live within an hour’s drive of Dublin, Ireland. Thereafter, data collection is phone-based. For the qualitative study component, interviews can be conducted in person or over the phone, depending on participant preferences.

### Sample

Quantitative component: Sample size was calculated to ensure that the study was sufficiently powered. Power in single-case experimental designs is a function of the following: sample size (number of observations per phase multiplied by number of participants), intraclass correlation (ratio of between-case variance to total, or within and between case variance), auto-correlation, effect size to be detected, and the nominal Type 1 error rate (
Shadish *et al.*, 2014a). A rigorous approach described by
Shadish and colleagues (2014a) to calculating sample size uses the alternative d-statistic to the traditional statistic used in between-subjects designs for single case designs. Our primary outcome of interest is health-related quality of life, which will be measured using the EQ-5D scale (see Outcomes). The minimally important difference in this scale has previously been calculated as 0.074 (
Walters & Brazier, 2005) and norms of the EQ-5D have yielded a standard deviation of 0.23 (
Kind *et al.*, 1999). These figures were used to estimate an effect size (using Shadish’s alternative d-statistic) of 0.32. Using this figure in a simulation macro provided by
Shadish and colleagues (2014a), with intraclass correlation set to a conservative estimate of 0.5, autocorrelation set to same, and alpha set to 0.05 for a multiple baseline design) with 13 observations (i.e. a period of six months, specified to be at least two observations in “A” phase, and the rest in “B” phase) per participant, and desired power of 0.8, a sample size of 85 is required. This sample size also provides sufficient power (0.9) for the secondary outcome (brain health), calculated using the same approach described above.

Qualitative component: 10–15 befriendee-befriender pairs will be recruited via the collaborating organisation. Sample size estimation in constructivist grounded theory is guided by data review after 3–4 interviews are conducted to assess thematic saturation (
Charmaz, 2006).

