### Sample selection and recruitment

Quantitative component: Participant recruitment is purposive and non-probability. Participants are recruited via ALONE, a charity organisation based in Dublin who offer, among other services, a befriending service for older adults. Participants will be recruited from the pool of individuals who contact ALONE to enquire about these befriending services. Typically, such individuals are referred from other services (e.g. GP services) and a visit is arranged to discuss service uptake. For the period of the proposed study data collection, ALONE staff members will include two additional questions to their routine visits – whether individuals self-report as lonely, and whether they would be interested in participating in an evaluation of the services. If individuals wish to be involved, they will receive information followed by a phone call from the project research assistant. If the participant is screened as eligible for the study, and is willing to participate, an initial data collection appointment will be made (with fortnightly appointments to be scheduled following this point for the remainder of the participant’s involvement in the study, up to a total of 11 post-intervention data collection points, or a period of six months).

An average of 35 (range 18–66) individuals were referred to ALONE each month between May 2016 and April 2017 (with a positive trend in numbers, likely owing to increased recruitment efforts on the part of ALONE). Of these, a conservative estimate is that 50% (17) would be interested in receiving a befriending service. A recent evaluation of ALONE’s befriending service found that 40% of service users defined themselves as lonely prior to service uptake (
Burke, 2015). As such, 10 participants can be expected to self-identify as lonely, and thus be considered to be eligible for further screening into the study. Assuming a response rate of 50%, approximately five individuals could be recruited per month, meaning that the target of 85 participants is likely to be reached across 17 months of data collection. Given that six months are required as the follow-up period, this means that a minimum of 23 months’ data collection period is required.

Qualitative component: Participant recruitment is purposive, non-probability sampling, from those already using the befriending service.

Inclusion criteria for quantitative component:

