### Intervention

The intervention is a befriending service. This service provides companionship to older people who would like extra social contact, through a weekly visit from a volunteer befriender. The volunteer befriender provides companionship and small practical supports where necessary and appropriate. The timing of the weekly visit, along with the nature of these visits (e.g. activities the befriender-befriendee pair may wish to complete together), is agreed between the older person and their volunteer befriender. ALONE recruit volunteers to provide the befriending service. Recruitment, training, and perpetual support is offered by staff at ALONE whose remit is to manage the befriending service. ALONE also have staff members who discuss a range of potential services and benefits available in the community and through ALONE with the older adults who contact them. At this initial meeting, older adults are told about the befriending service and can opt in to receiving this service. If an older adult expresses interest in the befriending service, they are then told about the research study running concurrently with the service. They are told that the service is available to them regardless of whether they are interested in the research study, and that their involvement in the study has no bearing on their receipt of the service. If the older adults are interested at this point in the research study, ALONE staff request verbal consent to pass their contact details to the research team. ALONE befriending service staff contact the older adults to discuss the befriending service with them at this point. They are made aware that the goal is for service users to be matched to a befriender as soon as possible and that before this match takes place at least two observations will be made (one initial, and one after a period of two weeks, and thereafter). If a participant is matched before two observations are delivered, this means that the participant has exited the baseline period of the trial early and their data may be excluded from the final dataset. Participants are asked about any preferences they may have in relation to their befriender by ALONE staff, who then attempt to find a match for them. The befriending match also takes into account location of the service user and potential befriender. Once a match has been made, the service user is informed, and staff from ALONE accompany the befriender to the home of the service user for an initial visit. Adverse events arising from participants’ receipt of the befriending service will be the responsibility of ALONE, as is normal practice.

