### Adherence

In relation to involvement in the research study, the research assistants will make every effort to be flexible with their appointments for observations, which take place every two weeks. If participants miss observations, the research assistants will provide opportunities for additional observations at the end of the expected 26 weeks, and if this is not possible, and the participant is overly taxed with their engagement in the study, research assistants will suggest that they participate at least in the final time point (after 26 weeks) since our statistical modelling techniques can still garner trends based on these incomplete data. 

No prohibitions are placed on study participants or their befrienders during the trial. Since participants are linked in with general support coordinators over the course of their engagement with the trial, they may be in receipt of other services as requested/required. Support coordinators in ALONE link older adults with a range of nationally available services. The trial ends six months after registration for participants. However, the service persists for as long as participants require or desire. ALONE recommend a year-long commitment in the first instance to befrienders, so in most cases participants will retain their befriending service visits from the same volunteer. However, it is possible that befrienders will withdraw or that participants will request a change in befriender during the trial lifespan. In this event, data collection will continue, and the withdrawal or change in befriender will be modelled as a covariate in the statistical analysis.

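### The 85 participants calculated for 0.80 power are also the recruitment target, with no stated allowance for the losses the protocol itself foresees

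*Protocol article*

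**What the plan says.** The Sample section (quantitative component) takes a minimally important EQ-5D difference of 0.074 and a standard deviation of 0.23, giving an effect size of 0.32. Intraclass correlation and autocorrelation are both 0.5, alpha is 0.05, and each participant gives 13 observations, at least two of them in phase A. For a target power of 0.8, a published simulation macro then yields the result that "a sample size of 85 is required". Brain health is covered by the same number: "This sample size also provides sufficient power (0.9) for the secondary outcome (brain health").

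The section on sample selection and recruitment expects about five recruits a month and concludes that "the target of 85 participants is likely to be reached across 17 months of data collection".

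Three other places foresee lost data:

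- **Intervention.** If a participant is matched before two observations have been made, "the participant has exited the baseline period of the trial early and their data may be excluded from the final dataset".
- **Procedure (obtaining consent).** Participants may leave the study whenever they wish.
- **Adherence, and Data collection and management.** Missed observations are followed up, and extra ones are offered at the end. If that fails and the participant is overburdened, "research assistants will suggest that they participate at least in the final time point (after 26 weeks").

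The Adherence, Data collection and Analytic plan sections add that the model can handle incomplete data. No section changes the 85 or the two power figures on account of loss, or says that 85 already includes an allowance.

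**The concern.** A number calculated for complete participants is normally the number needed at analysis, and enrolment is set above it or the power is quoted at the number expected to remain. Here the two numbers are the same, while the protocol describes a route by which whole participants can drop out of the dataset and others by which records can be incomplete. The power quoted thus belongs to a fuller dataset than the plan expects to have. At stake is how a null result is read: it would be set against 0.80 power for the primary outcome and 0.9 for brain health, when the design with its expected losses offers less than that on the protocol's own reckoning.

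**Working it through.** **Inputs.** From the Sample section: difference 0.074, SD 0.23, alpha 0.05, power 0.80 (EQ-5D) and 0.9 (brain health) at 85 participants with 13 observations each, intraclass correlation 0.5, autocorrelation 0.5. From the recruitment section: five participants a month, 17 months. Sidedness is not stated; two-sided is assumed. Loss rates are assumed.

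**1. The plan's own figures.**

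- Effect size: 0.074 / 0.23 = 0.3217, which agrees with the stated 0.32.
- Recruitment: 5 × 17 = 85, equal to the calculated number, surplus zero.
- The 85 itself comes from a macro whose model is not printed. Closed-form analogues use N = ((1.960 + 0.842) / 0.32)² × v = 76.65 × v. Here v is the variance of one participant's phase effect, with total variance 1, within-person variance 0.5, autocorrelation 0.5, and two A and 11 B observations:

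| Model | v (GLS) | N (GLS) | v (OLS) | N (OLS) |
|---|---|---|---|---|
| Phase shift only | 0.341 | 26 | 0.427 | 33 |
| Plus linear trend | 0.484 | 37 | 0.623 | 48 |
| Level and slope change | 1.239 | 95 | 1.436 | 110 |

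None of these gives 85. The macro is not at hand, so this does not show 85 to be wrong. It does mean that everything below takes the protocol's statement that 85 gives 0.80 as given.

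**2. Power if 85 are enrolled and a fraction L contributes nothing.** Information is proportional to the number of participants, so the noncentrality shrinks by √(1 − L):

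Power = Φ((z₀.₉₇₅ + z_power) × √(1 − L) − 1.960)

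The starting noncentrality is 1.960 + 0.842 = 2.802 for EQ-5D and 1.960 + 1.282 = 3.242 for brain health.

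| Assumed loss L | Evaluable of 85 | EQ-5D | Brain health |
|---|---|---|---|
| 0 | 85 | 0.80 | 0.90 |
| 10% | 76.5 | Φ(2.658 − 1.960) = 0.757 | Φ(3.075 − 1.960) = 0.868 |
| 20% | 68 | Φ(2.506 − 1.960) = 0.707 | Φ(2.899 − 1.960) = 0.826 |
| 30% | 59.5 | Φ(2.344 − 1.960) = 0.650 | Φ(2.712 − 1.960) = 0.774 |

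**3. Small losses.** With four of 85 lost, √(81/85) = 0.976 and 2.802 × 0.976 = 2.735, so EQ-5D power is Φ(0.775) = 0.78. Brain-health power is still 0.80 at 25% loss.

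**4. Sidedness.** With a one-sided 0.05 test the starting noncentrality is 1.645 + 0.842 = 2.487. EQ-5D power is then Φ(2.359 − 1.645) = 0.76 at 10% and Φ(2.224 − 1.645) = 0.72 at 20%, so the illustration hardly depends on this assumption.

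**5. Partly observed participants.** No figure is given for them. It would need a within-person model, and the simple phase-shift model already gives 0.999 power at 85 by GLS, so it cannot be combined with the protocol's 0.80. The planned analysis is in any case a generalised additive model with a smooth trend, and two baseline observations are the minimum, not a fixed split.

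**The case against.** The strongest reply is that the planned model accepts incomplete records and unequal numbers of observations, that missed observations can be made up at the end, and that exclusion after an early match is possible, not certain. This stands in part: a missed call need not cost a participant, and loss may be small. But a model that tolerates gaps does not restore the information in them. The Sample section itself treats sample size as observations per phase multiplied by participants. A participant whose data are excluded contributes nothing under any model.

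A second reply is that this is a condensed article and that expected attrition may be justified in a fuller protocol. That would excuse a missing loss rate. It does not explain why the article prints one number both as the requirement and as the target.

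Some stronger readings are tempting but not supported:

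- A reader might infer that the stated power holds only if nobody is lost. Four losses cost about two percentage points, and brain-health power stays at 0.80 or above up to about 25% loss, although it is below the stated 0.9 after any loss.
- A reader might count withdrawal from the befriending service as lost data. The Intervention section invites those participants to carry on with data collection.
- A reader might take the fallback to mean that some participants supply a single observation. The final time point is requested in addition to whatever has already been collected.
- A reader might conclude that the study is underpowered. That cannot be shown: under a simple phase-shift model 85 would be ample, and under a level-and-slope model it would fall short before any loss.

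**Conclusion.** The point holds in a limited form. The calculated number and the recruitment target are identical, no allowance is stated, and the protocol foresees exclusion, study withdrawal and missed observations. On its own relation, 85 enrolled will give somewhat less than 0.80 for EQ-5D and less than 0.9 for brain health. For assumed whole-person losses of 10% to 20% the size is about 0.76 to 0.71 and 0.87 to 0.83 respectively. This rests on three things: the unverified statement that 85 gives 0.80 (and 0.9), the assumed loss rates, and lost participants contributing nothing. It is a fault in how the power is stated, and does not show that the trial will fail to answer its question.

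**What to change.** In the Sample section, state that 0.80 and 0.9 refer to 85 evaluable participants with complete data in both phases. Then give an expected loss with its basis, and report the power at 85 enrolled after that loss, obtained by rerunning the same simulation macro at the reduced number (for example 68 participants for a 20% loss). The approximate figures above are illustrations and should not be copied into the protocol in place of that run. If the base calculation is revised for other reasons, the same allowance should be carried over.

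No extra enrolment is proposed: the Study status section reports 49 recruited, and the Discussion says that the pandemic slowed recruitment. The cost is one rerun and one or two sentences, and a stated power that is less favourable.
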